### Study design

SMARTER is a prospective, randomized, open-label, blinded-endpoint (PROBE) trial comparing two strategies to increase physical activity among overweight/obese adults followed for DM2 and/or hypertension. Allocation is concealed with an intervention to allocation ratio of 1:1.

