### Measurements

All measurements detailed below are assessed both at baseline and following the intervention at one year so that changes during the trial may be computed. These evaluations are conducted at our Vascular Health Unit (Division of Internal Medicine, McGill University Health Centre).

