### Sample size

Madden and colleagues [25] conducted a randomized controlled trial comparing a 3-month supervised exercise program with usual care in adults with DM2, hypertension, and dyslipidemia. Exercise sessions were three times per week (cycle ergometers, treadmills). They demonstrated a 13.9% reduction in cfPWV in the intervention arm compared with a 4.4% increase in the control arm (i.e., an 18.3% difference). To be conservative, we aim to detect a 10% difference between our active and control trial arms to an accuracy of ± 5% over a one-year period. This implies that our CI for the difference will be narrow enough to rule out only trivial effects. Based on the report by Madden and colleagues, we estimate a standard deviation (SD) of 28 in the active treatment arm [standard error, SE* sqrt (n) = 6.7 * sqrt(17)] and 14 for the control arm [3.3*sqrt (17)]. Under these conditions, with ± 5% CI width, we will need to retain 151 per arm (i.e., 302 in total). Allowing for a loss to follow-up of up to 17% based on our previous studies, [50,51] we require a sample size of 364 individuals (i.e., 182 per arm).

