### Statistical analysis

Our main outcome is percentage change in arterial stiffness (i.e., cfPWV) within each trial arm. We will calculate mean between trial arm differences in “after minus before changes”, with 95% CIs (intent-to-treat analysis). In addition to examining between trial arm differences in percentage change from baseline arterial stiffness, we will also evaluate between arm absolute differences in raw “after minus before changes” in cfPWV. Although trial arms are likely to be similar at baseline, we may use a linear model to adjust for any possible differences between arms for important covariates (e.g., baseline daily steps, baseline BMI, age, sex, changes in medications). If relevant, in a sensitivity analysis, we will use multiple imputation to impute missing data. A similar approach will be used to examine between-arm differences in daily steps and vascular risk factors. We will also correlate increments in steps to changes in arterial stiffness, anthropometric parameters, and specific vascular risk factors. Finally, we may employ additional secondary analyses (e.g., per protocol analyses; analyses in DM2 alone, hypertension alone, DM2 and hypertension; analyses in participants with and without medication changes).

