We are aware of some potential limitations to the trial. Firstly, physicians cannot be blinded to the intervention given that they are delivering it. However, outcome assessors are blinded to intervention arm status, and both the primary outcome and most of the secondary outcomes are evaluated objectively (i.e., assays or automated measurements). We acknowledge the possibility of contamination of the control arm: that is, physicians may be tempted to employ the SMARTER intervention in the control arm, particularly if they perceive benefit. However, only the active trial arm receives pedometers at the onset of the intervention period. Following the final trial evaluation, the control trial arm participants will be provided with a pedometer in gratitude for their participation, and they will be free to engage in a step count prescription strategy with their treating doctor. This ‘delayed’ intervention may facilitate adherence to study procedures. Physicians are free to modify medications during the trial period and this could impact some outcomes. To address this possibility, we will perform secondary analyses with (i) adjustment for changes in medications and (ii) restriction to participants without such changes. We acknowledge that more frequent contact with physicians and/or other health care team members could strengthen the impact of the intervention; however, DM2 and hypertension follow-up frequently occurs in settings without multidisciplinary teams and the demands of clinical care may render more frequent contact challenging. We have, therefore, designed our intervention to be ‘pragmatic’ with 3 to 4 follow-up visits over one year accompanied by a written prescription. Patients with DM2 and hypertension generally have common features including insulin resistance and increased risk for vascular disease. The inclusion of participants with DM2 and hypertension, each alone or in combination, allows us to achieve recruitment targets in a reasonable time frame and to generalize our results to groups of patients seen frequently in clinical practice; we will nonetheless perform subgroup analyses (DM2 alone, hypertension alone, DM2 and hypertension in combination).

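### The primary comparison is labelled intent-to-treat but, as written, compares retained participants without adjustment; all randomised participants enter only through a conditional imputation sensitivity analysis

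*Protocol article*

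**What the plan says.** The Statistical analysis section of the protocol article defines the outcome: "Our main outcome is percentage change in arterial stiffness (i.e., cfPWV) within each trial arm". The arms are compared on mean before-to-after change, "with 95% CIs (intent-to-treat analysis"). Covariate adjustment is left open: "we may use a linear model to adjust for any possible differences between arms for important covariates". The examples of covariates do not include baseline cfPWV. The only sentence on missing data is "If relevant, in a sensitivity analysis, we will use multiple imputation to impute missing data".

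Two other sections decide what this means in practice. Under Measurements, everything is "assessed both at baseline and following the intervention at one year", so there is no interim cfPWV. Under Sample size, the precision target is tied to completers: "we will need to retain 151 per arm (i.e., 302 in total"). That number is then inflated to 364 to allow for loss of up to 17%.

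**The concern.** With two assessment times and a change score as outcome, a participant who misses the one-year visit contributes nothing to the main comparison unless a value is imputed, and imputation is assigned to a sensitivity analysis. The label and the analysis therefore do not cover the same people. The label suggests everyone randomised; the calculation uses those who came back.

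An unadjusted comparison of completers estimates the effect in all randomised participants only if missingness is unrelated to change in cfPWV within each arm, or if the distortions cancel between arms. The article does not state either condition. Adjustment for baseline predictors of loss would weaken the condition, but it is not committed. The arms differ in what is asked of participants and the trial is open-label, so different patterns of loss are possible. At stake is the accuracy of the primary estimate, and of a confidence interval designed to be only 5 points wide on each side.

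**Working it through.** **Inputs from the Sample size section.** SD 28 (active) and 14 (control); CI half-width 5 points; target difference 10 points; loss up to 17%; 151 retained and 182 randomised per arm. Allocation is 1:1 (Study design).

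**1. Reproduce the plan's figures.**
- n per arm = (1.96 / 5)² × (28² + 14²) = 150.6, rounded up to 151.
- Inflated for loss: 151 / 0.83 = 181.9, rounded up to 182 per arm, 364 in total.

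Both agree with the article. The half-width with 151 per arm is 1.96 × √(980 / 151) = 4.99, so the planned precision is that of completers. The sample size is not in question.

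**2. Who may be left out.** 364 − 302 = 62, and 62 / 364 = 17.0%. This is the planning ceiling, not observed attrition.

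**3. Bias of the completers' estimate.** Let d be the proportion lost in an arm, and g the number of points by which the mean percentage change of its dropouts is worse than that of its completers. Measured as benefit to the active arm, relative to all randomised participants:

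bias = d(active) × g(active) − d(control) × g(control)

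The gaps and the unequal loss rates below are assumptions; the documents give none. A gap of 10 in the active arm alone means that dropouts there get none of the planned effect.

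| Loss, active / control | Gap, active / control | Bias (points) | Share of 5-point half-width |
|---|---|---|---|
| 17% / 17% | 5 / 0 | 0.17 × 5 = 0.85 | 17% |
| 17% / 17% | 10 / 0 | 0.17 × 10 = 1.70 | 34% |
| 17% / 17% | 10 / 10 | 1.70 − 1.70 = 0 | 0% |
| 25% / 9% | 10 / 10 | 2.50 − 0.90 = +1.60 | 32% |
| 9% / 25% | 10 / 10 | 0.90 − 2.50 = −1.60 | 32%, against the active arm |

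**4. Effect on the interval.** The standard error with 151 per arm is √(980 / 151) = 2.55. A bias of 1.70 is 0.67 standard errors, and coverage of a nominal 95% interval falls to about 89.8%. For a bias of 0.85 it is about 93.7%.

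**The case against.** The best reply is that this is a condensed article with a common layout: observed outcomes analysed by assigned arm, with imputation as a check. Intent-to-treat may simply mean analysed as randomised regardless of adherence, since the same section lists per-protocol analyses separately. The imputation sentence says the authors will do it, and its opening condition most naturally means if data are missing, so the analysis is conditional and not discretionary. Imputation details could sit in a statistical analysis plan that is not shown. All of this is fair. It does not remove the point, because the article itself chooses where imputation goes, and that choice leaves dropouts out of the primary estimate.

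Three stronger readings are tempting and are not supported.

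- **That the bias favours the active arm.** A reader might infer this from the thought that participants who miss step targets leave. The documents do not show it. Under Interventions, later prescriptions follow the counts achieved and individual circumstances. The Discussion says that after the final evaluation "the control trial arm participants will be provided with a pedometer in gratitude for their participation", which is a retention measure for the arm without the device and could as well balance loss as unbalance it.
- **That the bias could reach a third of the target effect.** Gaps of 15 or 20 points would give 0.17 × 15 = 2.55 or 0.17 × 20 = 3.4. With a planned effect of 10, they require active dropouts to fare 5 to 10 points worse than controls, while control dropouts do not differ from control completers at all.
- **That the plan never examines outcome-related dropout.** The article names no such analysis, but its silence does not show that the full plan lacks one.

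It is also true that imputation under missing-at-random does not cure outcome-dependent loss. With a single post-baseline measurement it adds to a baseline-adjusted observed-case model only through auxiliary variables.

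**Conclusion.** The concern holds in this form: the comparison labelled intent-to-treat is, as written, an unadjusted analysis of retained participants, with up to 62 of 364 (17.0%) outside it. That retained participants alone are used is not stated in so many words. It follows from the change-score outcome, the two assessment times, the precision calculation based on retained numbers, and the place given to imputation.

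Bias is possible, not established, and its direction is unknown. The illustration of 1.7 points (34% of the planned half-width) assumes the full 17% loss, active dropouts who get none of the planned effect, and control dropouts who resemble control completers. The bias is zero when the product of loss and gap is the same in both arms. This is large enough, in the primary analysis, to justify a change that needs no new data.

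**What to change.** - **Primary estimate.** Define it on all 364 randomised participants, from a model adjusted for baseline cfPWV and prespecified baseline covariates, under a stated missing-at-random assumption. Use multiple imputation by arm, with baseline variables (such as age, sex, BMI, blood pressure, daily steps and diagnosis) and auxiliary data available in both arms, such as clinic visits completed. Step logs are described only for the active arm, so log-book use can serve only within that arm's imputation model.
- **Wording.** Remove the condition that opens the imputation sentence, and say which participants the intent-to-treat label covers.
- **Supportive analysis.** Report the observed-case result beside the primary one.
- **Sensitivity analysis.** Commit to a delta-adjusted analysis that varies the assumed outcome of dropouts separately in each arm, since neither the direction nor the arm can be presumed. It should show how large the departure must be to alter the conclusion.

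The cost is revised wording and modest programming. The variables named are already collected, and sample size, visits and measurements do not change. The downside is a slightly more complex primary analysis. Imputation will not recover the 4.55-point half-width that complete follow-up would give (1.96 × √(980 / 182)). What it offers is a weaker missingness assumption, stated openly and then tested.

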## Discussion

The SMARTER trial is testing an innovative step count prescription strategy delivered by physicians to their patients with DM2 or hypertension. The focus on daily step counts arguably simplifies the process of physical activity prescription. Increasingly, physicians and patients are partners in monitoring and managing chronic diseases. Such partnerships can improve patient adherence and health outcomes [15]. Less than one third of North Americans achieve the recommended 10,000 steps/day [52] and we have demonstrated that in adults with DM2 and/or hypertension, mean counts are low at approximately 5,000 steps/day, with a further 15% reduction during fall and winter months [50]. “Re-engineering” walking into daily life could be an effective means of improving the arterial health of patients with DM2 and/or hypertension.

The effects of the SMARTER intervention are being determined in terms of biological impact, particularly in terms of changes in arterial stiffness as captured by cfPWV. In the Framingham Heart Study, a one SD increment in arterial stiffness was associated with a 48% increase in arterial disease risk, independently of individual vascular risk factors [23]. A meta-analysis indicates that an increase in cfPWV by 1 m/s corresponds to an age-, sex-, and risk factor-adjusted risk increases of 14%, 15%, and 15% in total cardiovascular disease event rates, cardiovascular mortality, and all cause mortality, respectively [53]. A recent analysis of the Framingham Offspring study demonstrated that higher aortic stiffness is associated with higher risk of incident hypertension [24], suggesting that in some cases stiffness precedes the development of hypertension. Illustrating the responsiveness of cfPWV to higher activity levels, a trial among older patients with vascular risk factors including DM2 demonstrated a 3-month supervised exercise program to confer an important reduction in cfPWV compared to usual care alone [25].

We are aware of some potential limitations to the trial. Firstly, physicians cannot be blinded to the intervention given that they are delivering it. However, outcome assessors are blinded to intervention arm status, and both the primary outcome and most of the secondary outcomes are evaluated objectively (i.e., assays or automated measurements). We acknowledge the possibility of contamination of the control arm: that is, physicians may be tempted to employ the SMARTER intervention in the control arm, particularly if they perceive benefit. However, only the active trial arm receives pedometers at the onset of the intervention period. Following the final trial evaluation, the control trial arm participants will be provided with a pedometer in gratitude for their participation, and they will be free to engage in a step count prescription strategy with their treating doctor. This ‘delayed’ intervention may facilitate adherence to study procedures. Physicians are free to modify medications during the trial period and this could impact some outcomes. To address this possibility, we will perform secondary analyses with (i) adjustment for changes in medications and (ii) restriction to participants without such changes. We acknowledge that more frequent contact with physicians and/or other health care team members could strengthen the impact of the intervention; however, DM2 and hypertension follow-up frequently occurs in settings without multidisciplinary teams and the demands of clinical care may render more frequent contact challenging. We have, therefore, designed our intervention to be ‘pragmatic’ with 3 to 4 follow-up visits over one year accompanied by a written prescription. Patients with DM2 and hypertension generally have common features including insulin resistance and increased risk for vascular disease. The inclusion of participants with DM2 and hypertension, each alone or in combination, allows us to achieve recruitment targets in a reasonable time frame and to generalize our results to groups of patients seen frequently in clinical practice; we will nonetheless perform subgroup analyses (DM2 alone, hypertension alone, DM2 and hypertension in combination).

We have developed our trial in collaboration with physicians who manage DM2 and hypertension. We held several meetings with over 24 physicians to discuss the intervention. They underscored their need for physical activity promotion tools and viewed the SMARTER strategy to be feasible and easily integrated into clinical practice. They, nonetheless, expressed the need for Level A evidence as derived through a randomized controlled trial. This integrated knowledge translation approach will facilitate future knowledge translation efforts. If effectiveness is demonstrated, we are well-positioned to consider inclusion in Clinical Practice Recommendations for DM2 and hypertension.

The SMARTER intervention is novel in several respects: (i) It is physician-specific intervention that may be particularly important in understaffed clinics without the support of a full multidisciplinary team. (ii) A specific, signed, stamped written prescription is provided, focusing on step count targets. (iii) The rate of step count titration is individualized, based on baseline step counts, leveraging an existing therapeutic alliance. (iv) The primary outcome is change in arterial stiffness, a summative indicator of arterial health. Prior pedometer-based intervention studies have examined specific individual vascular risk factors but to our knowledge, none have evaluated a summative indicator of arterial health (arterial stiffness) as the primary outcome. (v) A shortcoming of prior studies has often been a lack of attention to medication use. This is being carefully recorded during our trial and we will perform subgroup analyses in those with and without medication changes (e.g., antihypertensive agents, antihyperglycemic agents, lipid-lowering agents). We will further evaluate changes in medication use as a secondary outcome. (vi) This will be one of the largest pedometer intervention trials ever conducted (364 participants).

In summary, the potential impact of the SMARTER intervention relates not only to the use of pedometers but rather to its incorporation into clinical care, leveraging the physician-patient therapeutic alliance. A key strength of the SMARTER trial is the ability to capture biological impact through measurement of arterial stiffness. Demonstration of effectiveness of the SMARTER intervention has strong potential to lead to wide and sustained adoption in clinical practice with integration in DM2 and hypertension management.

## Abbreviations

BMI: Body mass index; DM2: Type 2 diabetes; CI: Confidence interval; cfPWV: Carotid femoral pulse wave velocity; PWA: Pulse wave analysis; PWV: Pulse wave velocity; ECG: Electrocardiogram; VO2max: Maximum oxygen uptake; HDL-C: High density lipoprotein cholesterol; LDL-C: Low density lipoprotein cholesterol; Hemoglobin A1C: Glycosylated hemoglobin; HPLC: High performance liquid chromatography; MET: Metabolic equivalent; CVD: Cardiovascular disease
